### Objectives

The main objective of the present study is to investigate the effectiveness of the age-sensitive telehealth group psychotherapy (VISION-AGE) for older adults with depression (with or without comorbid anxiety) compared to a non-clinical active control condition (a group discussion programme) with regard to depression, anxiety, and psychological wellbeing. Furthermore, the mechanism of action of VISION-AGE will be investigated. Adaptive self- and developmental regulation strategies (defined as positive self-perceptions of ageing, reminiscence, life management, and future planning) are examined as mediators, based on the assumption that strengthening these capacities play a central role in reducing symptoms of depression and anxiety, while enhancing psychological well-being. The influence of comorbidity and the severity of depressive symptoms on the programme’s effectiveness will be explored through exploratory analyses. A mixed-methods approach is applied to relate older patients’ subjective experiences of change processes during the psychotherapy (as assessed by semi-structured interviews) to their psychometric treatment outcomes.

This large-scale superiority RCT is expected to provide robust evidence in support of the hypothesis that the intervention improves patient outcomes, thereby offering valuable guidance for the development of future healthcare policies. Consequently, the intervention is accompanied by a health economic evaluation. The hypotheses and questions to be examined in the study are presented in Tables 1 and 2.

**Table 1 Tab1:** Overview of hypotheses in sub-study 1 (quantitative component of the mixed-methods design)

Hypothesis	Description
Main Hypothesis 1 H1a H1b	Our videoconference-based group-psychotherapy programme VISION-AGE (i.e., enriched LRT intervention group, IG) leads to greater reduction in • self-reported depression symptoms (primary outcome) and • clinician-rated depression symptoms (secondary outcome) compared to a videoconference-based non-clinical group discussion programme (i.e., active control group, CG) at post-treatment and 6-month FU, with moderate between and moderate-to-large within effect sizes for VISION-AGE, while we assume that both conditions lead to significant reduction in depression over time.

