Hypothesis 2 H2a H2b	The VISION-AGE programme leads to • a greater reduction in anxiety symptoms and • a greater improvement in psychological well-being compared to the active control group at post-treatment and 6-month FU.
Hypothesis 3 H3a H3b H3c H3d H3e	The effectiveness of VISION-AGE is mediated by an improvement of self- and developmental regulation, as assessed in a standardized manner (i.e., • positive self-perceptions of ageing, • reminiscence, • life management, • future planning as mechanisms of action). The effect is most pronounced respectively in those participants who had lower baseline scores in these variables.

**Table 2 Tab2:** Research questions in the mixed-methods design (quantitative and qualitative)

Research question	Description
Research question 1	Which subjectively experienced processes of change arise in the participants everyday life by participating in VISION-AGE?
Research question 2	How are the subjectively experienced processes of change related to the primary outcome?
Research question 3	Merging the results from study 1 and 2 (triangulation): How effective is VISION-AGE, and what are objective (measured via standardized instruments) and subjective (in the participants’ personal experience) mechanisms of action?
Research question 4	Explorative cost-effectiveness analysis: How cost-effective is VISION-AGE compared to the CG?

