### Power and sample size

The study will aim to include 250 participants, with 125 allocated each to the IG and the CG, thereby ensuring a minimum of 100 completed data sets for each intervention at the FU. The plan is founded upon a priori sample size calculation, which yielded a total of 200 participants following a 1:1 randomisation ratio. However, the drop-out-rate must also be considered, which is estimated at 20%, based on the findings of previous studies, for example, 17% in a study with older adults experiencing depression and anxiety [36].

The sample size calculation is based on the assumption of a medium-to-large pre-post (“within”) effect size (d = 0.75) for VISION-AGE and a moderate “between” effect size (d = 0.45) for the contrast (pre-post change in the IG compared to pre-post change in the CG). It is hypothesised that the proposed programme, considered an enhanced form of LRT, will demonstrate effect sizes that are at least commensurate with those observed in LRT, and approximately equivalent to those reported for CBT: The large pre-post effect size, as found for CBT (d = 1.06) and LRT (d = 1.0) in late-life depression [16] will somewhat be reduced due to the possible comorbidity with anxiety and the video-based format (e.g., g = 0.79 for depression and g = 0.82 for anxiety, meta-analysis) [33]. The group setting additionally reduces the effect size in late-life depression (e.g., d = 0.65) [39]. However, since we are planning very small groups and additional individual sessions, we estimate a within effect size of no less than d = 0.75 and a between effect size of d = 0.45.

For statistical tests on the α = 5% level, with a total sample size of *N* = 200 (100 per arm), power simulations using R package Superpower [40] yielded a power > 0.90 for both main effect and the interaction regarding a 2 (condition) by 2 (time) mixed Analysis of variance (ANOVA), as well as power > 0.80 for the main contrast of interest (i.e., the pre-post change in the IG in comparison to the pre-post change in the CG).

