### Statistical analysis sub-study 1 (quantitative study)

Statistical analyses regarding sub-study 1 will be based on intention-to-treat (ITT) as well as on per-protocol analyses. The primary analysis will be ITT. To compensate for panel attrition and item-nonresponse, missing data will be multiply imputed in all ITT analyses. Imputation models will be fully compatible to the subsequent analysis models (i.e., substantive model compatible multiple imputation) and will include all relevant associations (like interaction terms) and will represent the clustered structure of the data. The main substantive model of interest is a (generalized) linear mixed effects model, which evaluates stability and change in the outcome variables over time depending on experimental condition. The focal effect of interest in this model is the time by condition interaction. To interpret this effect, we especially look at the following contrast: the pre to post change in the experimental condition in comparison to the pre to post change in the control condition (i.e., a contrast over two contrasts). Additionally, pre-post and pre-FU effect sizes (Cohen’s d) will be calculated for all outcome-variables for both groups (IG and CG) to further quantify the found effects. In additional (exploratory) analyses, we will test for possible effects of gender, age, education, comorbidity and severity of comorbid symptoms. We also explore possible interactions of the outcome variables by means of parallel longitudinal path modelling. If the first two hypotheses can be confirmed, hypothesis 3 (regarding the underlying therapeutic mechanisms) will be evaluated by mediation and moderation analyses using path models.

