### Statistical analysis sub-study 2 (qualitative study)

The question of sub-study 2 is which subjective processes of change the IG participants experience in everyday life as a result of participating in VISION-AGE (step 1; qualitative approach), and how these changes are associated with quantitative therapy outcomes (step 2; quantitative approach).

In step 1, a selection of IG participants are asked about their subjective experiences in structured, qualitative interviews. In accordance with the principle of maximum variation within the sample, the IG participants who are interviewed will have achieved different outcomes in the post-treatment (i.e. participants who improved as well as those who deteriorated). We estimate that roughly 20 IG participants will be needed to reach theoretical saturation. The interviews will be recorded on video and fully transcribed. Through qualitative content analysis categories will be developed based on the written material. These categories will represent different types of subjective processes of change, such as ‘rediscovering resources’ and ‘defining life goals’. Based on these categories, shorter, more focused, problem-centered interviews will be conducted with all remaining IG participants (approximately 80 at the post- treatment stage, considering drop-outs), asking specifically about the identified categories.

In step 2, it is recorded for each IG participant whether various categories of subjective change processes apply to them (yes/no). Additionally, an individual frequency score (i.e. how often each category is used) and an individual diversity score (i.e. the number of categories used at least once) are calculated for each IG participant [35].

### Triangulation of sub-study 1 and 2

To gain a deeper understanding, findings from sub-studies 1 and 2 are triangulated by relating the categories of subjective change processes identified in the qualitative analysis of sub-study 2 to the mediators identified in sub-study 1 [35]. Finally, those subjective and objective processes of change that have been proven as the best predictors in the respective sub-study (i.e., 1 and 2) are statistically put in relation in terms of their predictive power in a common regression model.

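### The mediation analysis (H3) is run only if H1 and H2 are both confirmed, although the mechanism aim is stated without condition and the triangulation needs its result

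*Protocol article*

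**What the plan says.** Under Statistical analysis sub-study 1 the protocol article sets the rule: "If the first two hypotheses can be confirmed, hypothesis 3 (regarding the underlying therapeutic mechanisms) will be evaluated by mediation and moderation analyses".

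The two preceding hypotheses are in Table 1. H1 has two parts, self-reported depression (PHQ-9, primary) and clinician-rated depression (MADRS, secondary), claimed "at post-treatment and 6-month FU, with moderate between and moderate-to-large within effect sizes". H2 also has two parts, anxiety and psychological well-being, "compared to the active control group at post-treatment and 6-month FU". The article does not say whether confirming a hypothesis means both parts or one, or both time points or one.

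The Objectives section attaches no such condition: "Furthermore, the mechanism of action of VISION-AGE will be investigated". The Abstract and the registered title likewise name mechanisms or modes of action next to efficacy. The Discussion says the study examines whether strengthening the four mediating strategies is decisive for symptom relief.

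Under Triangulation of sub-study 1 and 2, the qualitative categories are to be related "to the mediators identified in sub-study 1", and the best predictors from both sub-studies then enter one regression model. No provision is made for the case in which sub-study 1 has identified no mediators because H3 was not run.

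**The concern.** The rule, the objective and the triangulation do not fit together. The objective promises an analysis that the analysis section may withhold, and a later step needs the output of the withheld analysis.

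The precondition is also wider than its purpose requires. On its plain reading, a non-significant result for well-being would stop the examination of how a demonstrated PHQ-9 effect came about, although it carries no information on that pathway. Nor does an indirect effect require a significant total effect. Because 'confirmed' is undefined, whether H3 is evaluated could be settled after the results are known.

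The unfavourable case is realistic on the article's own account. Its Background cites a recent late-life CBT trial that was not superior to supportive therapy, and notes that superiority of group therapy over active controls was not shown in all studies. Mediator data from both arms would then help to separate targets that did not move from targets that moved without relieving depression.

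**Working it through.** **Inputs from the article (Power and sample size).** Tests "For statistical tests on the α = 5% level"; 200 analysed, 100 per arm; between-arm effect d = 0.45, one figure not tied to a particular outcome; stated power above 0.80 for the main contrast.

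**Assumptions, not in the article.** Two-sided tests; d standardised on the SD of change; the same d for every outcome and time point unless stated; one common correlation ρ between any two test statistics, shown from 0.3 to 0.7; 'confirmed' means every component significant.

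**Step 1: the plan's own figure.** The expected test statistic is δ = d·√(n/2) = 0.45·√50 = 3.182. Power = Φ(3.182 − 1.960) = Φ(1.222) = 0.889 (0.886 with the noncentral t). This agrees with the stated power above 0.80. If H3 depended on PHQ-9 alone, it would not be run in 1 − 0.889 = 0.111 of trials.

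**Step 2: all components must succeed.** For k tests with common correlation ρ,

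P(all significant) = ∫ φ(u) · [Φ((δ − 1.960 + √ρ·u)/√(1 − ρ))]^k du.

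k = 4 is PHQ-9, MADRS, anxiety and well-being at post-treatment; k = 8 adds the same four at follow-up.

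| ρ | k = 4: H3 run | k = 4: not run | k = 8: H3 run | k = 8: not run |
|---|---|---|---|---|
| 0.3 | 0.679 | 0.321 | 0.524 | 0.476 |
| 0.5 | 0.719 | 0.281 | 0.606 | 0.394 |
| 0.7 | 0.763 | 0.237 | 0.689 | 0.311 |

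**Step 3: H3 blocked although PHQ-9 succeeded.** P(not run | PHQ-9 significant at post-treatment) = 1 − P(all significant)/0.889.

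- k = 4: 1 − 0.679/0.889 = 0.236 at ρ = 0.3; 1 − 0.763/0.889 = 0.142 at ρ = 0.7.
- k = 8: 1 − 0.524/0.889 = 0.410 at ρ = 0.3; 1 − 0.689/0.889 = 0.225 at ρ = 0.7.

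**Step 4: sensitivity, as the probability that H3 is run, ρ from 0.3 to 0.7.**

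- Power exactly 0.80 per test, the article's floor: k = 4, 0.50 to 0.62; k = 8, 0.33 to 0.53. An intraclass correlation of 0.10 within the groups of four, if it acted in both arms, would bring single-test power to about this level (design effect 1 + 3·0.10 = 1.3; power 0.80).
- H1 outcomes at d = 0.45 and H2 outcomes at an assumed d = 0.35 (power 0.70 each): k = 4, 0.46 to 0.57; k = 8, 0.29 to 0.47.
- H2 outcomes at an assumed d = 0.30 (power 0.56 each): k = 4, 0.33 to 0.43; k = 8, 0.17 to 0.33.

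**Step 5: what does not depend on the rule.** Table 3 schedules the mediators in both arms whatever the outcome. Research questions 1 and 2, on subjectively experienced change and its relation to the primary outcome, carry no precondition. Only H3, and the use of its result in research question 3, depend on it.

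**The case against.** The rule has a rationale. H3 is worded as mediation of the programme's effectiveness, which presupposes that there is some, and the objectives link the mediators to anxiety and well-being as well as to depression. Testing mechanisms after efficacy is a recognised order. This stands as a reason for a hierarchy in how H3 is labelled. It does not justify withholding the estimates, or letting a secondary outcome block mediation of the primary one.

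The strict reading of 'confirmed' is not stated either. The contrast singled out in the analysis section is pre to post, and for follow-up it names only effect sizes; an operational definition may be in an SAP that is not shown. This also stands, and is why both readings are given. It does not remove the mismatch with the unconditional aim and the triangulation, since both H1 and H2 are required on any reading.

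A reader might infer that the mechanism aim will probably go unanswered even if the therapy works as planned. The documents do not support that. At the planned d = 0.45 and correlations of 0.3 to 0.7, H3 is run in most trials on either reading (0.68 to 0.76, or 0.52 to 0.69). Non-evaluation becomes more likely than not only with added assumptions, such as smaller effects on anxiety and well-being, or all eight tests required with power near 0.80. Nor would the mediator measures be wasted: they are collected, and the article does not forbid exploratory use.

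**Conclusion.** The point holds as an internal inconsistency with a material, but not overwhelming, risk. The article makes H3 depend on H1 and H2 together, states the mechanism aim without that condition, and gives the triangulation no fallback. This part rests on the text alone.

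The size rests on assumptions about correlation, sidedness and the meaning of 'confirmed'. With d = 0.45 throughout, H3 is not run in roughly one trial in four to one in three (four tests), or one in three to just under one in two (eight tests), compared with about one in nine if only PHQ-9 mattered. Smaller effects on anxiety or well-being, or clustering within groups, raise these figures. What would be lost is the quantitative mediation result and the part of the triangulation built on it; the data and the qualitative findings on change processes would remain.

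**What to change.** Remove the joint precondition. State that the mediation path models are estimated in all cases, with intervals for the path from arm to mediator, the path from mediator to outcome, and the indirect effect. If a hierarchy is wanted, treat H3 as confirmatory only when the primary PHQ-9 contrast is significant and as exploratory otherwise. The triangulation then always has its input, and should say that it uses these estimates with the label they carry. The exact specification of the path models can stay with the SAP.

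The cost is a change of wording in the protocol and SAP before data are analysed. Visits, instruments and sample size are unchanged.

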### Statistical analysis sub-study 2 (qualitative study)

The question of sub-study 2 is which subjective processes of change the IG participants experience in everyday life as a result of participating in VISION-AGE (step 1; qualitative approach), and how these changes are associated with quantitative therapy outcomes (step 2; quantitative approach).

In step 1, a selection of IG participants are asked about their subjective experiences in structured, qualitative interviews. In accordance with the principle of maximum variation within the sample, the IG participants who are interviewed will have achieved different outcomes in the post-treatment (i.e. participants who improved as well as those who deteriorated). We estimate that roughly 20 IG participants will be needed to reach theoretical saturation. The interviews will be recorded on video and fully transcribed. Through qualitative content analysis categories will be developed based on the written material. These categories will represent different types of subjective processes of change, such as ‘rediscovering resources’ and ‘defining life goals’. Based on these categories, shorter, more focused, problem-centered interviews will be conducted with all remaining IG participants (approximately 80 at the post- treatment stage, considering drop-outs), asking specifically about the identified categories.

In step 2, it is recorded for each IG participant whether various categories of subjective change processes apply to them (yes/no). Additionally, an individual frequency score (i.e. how often each category is used) and an individual diversity score (i.e. the number of categories used at least once) are calculated for each IG participant [35].

### Triangulation of sub-study 1 and 2

To gain a deeper understanding, findings from sub-studies 1 and 2 are triangulated by relating the categories of subjective change processes identified in the qualitative analysis of sub-study 2 to the mediators identified in sub-study 1 [35]. Finally, those subjective and objective processes of change that have been proven as the best predictors in the respective sub-study (i.e., 1 and 2) are statistically put in relation in terms of their predictive power in a common regression model.

### Cost-effectiveness

An analysis of economic gains will be conducted by calculating the incremental cost-effectiveness ratio, defined as the difference in total costs divided by the difference in effect between the IG and the CG. The effect will be operationalized in terms of quality-adjusted life years (QALYs). To assess QALYs, the EQ-5D-5L [57] will be used, covering five dimensions—mobility, self-care, usual activities, pain/discomfort, and anxiety/depression—each with five levels of functioning: no problems, slight problems, moderate problems, severe problems, and extreme problems/unable to.

## Discussion

VISION-AGE is a large, nationwide superiority RCT to investigate the effectiveness and mechanisms of action of online group psychotherapy for older adults with clinically significant depression symptoms and partially comorbid anxiety in Germany. This approach is intended to address existing research gaps while facilitating a systematic analysis of both quantitative and qualitative developments throughout the programme’s duration. This systematic analysis is underpinned by the implementation of a mixed-methods design. The VISION-AGE programme builds on evidence-based therapeutic strategies from LRT, incorporating additional features proven to be helpful in self- and developmental regulation, as well as techniques from CBT and PP.

The therapeutic concept of the VISION-AGE manual is based on the strengthening of four self-regulatory resources, which will be examined as mediator variables. In the first step, participation in the program is expected to foster a more positive attitude toward one’s own ageing while reducing self-directed ageism. In the second step, the intervention aims to facilitate a balanced review of the patient’s life. In the third step, the training of SOC-strategies is intended to enhance life-management skills. In the fourth step, within the framework of the manual, participants are encouraged to actively engage with future-related issues and potential anxieties, thereby strengthening their capacity to plan for upcoming challenges. In this way, the ‘time corridors’ past - present - future are intensively discussed, whereby the latter has received little attention in previous therapeutic approaches. The group component is expected to further promote the ability to build relationships, develop trust, and strengthen both generational identity (based on being born in the same historical period) and age identity (based on sharing a similar life stage). These factors have a direct mood-enhancing impact, and thereby potentially improve mental and physical health.

It is hypothesised that VISION-AGE is more effective than an active control group, designed to resemble a typical social group in settings such as social care, at reducing symptoms of depression. The study examines whether strengthening the four mediating strategies is a decisive developmental step in alleviating depression and anxiety symptoms and enhancing participants’ well-being. Additionally, qualitative interviews provide insight into the change processes from the participants’ perspectives. These can provide new insights into important concepts that may not have been previously considered.

Together, the age-adapted structure of the manual and the comprehensive, multidimensional outcome assessment (both quantitative and qualitative) reflect the programme’s broad scope and its potential to promote holistic, active, and positive living in later life. The study results will provide insights into whether older adults accept online group therapy and to what extent they benefit from it.

Despite its promising theoretical foundation and practical relevance, the VISION-AGE study has some potential limitations. First, a selection bias may occur because participation requires basic IT skills; as a result, younger (under 80), more educated, or more motivated individuals may be overrepresented, which could limit the generalisability of the findings. Second, while the small group size is intended to foster intimacy and openness, it also increases the likelihood that individual participants will have a disproportionately strong influence on the perceived group cohesion and overall group dynamics. Third, although we believe that the economic, social, and ethical advantages of online group therapy outweigh its disadvantages, this specific delivery format might underestimate the effect of the VISION-AGE programme. Fourth, the intervention targets older adults with depressive symptoms, with or without comorbid anxiety, which may limit the generalisability of the findings to younger cohorts or older adults with different disorders.

